**4.1.4 Between the first and second meetings**

Pharmacists will be asked to use all of the material they obtain from their previous time in the practice, to prepare a tailored learning/action plan for each individual GP/nurse and the practice. A printed report of the plan will be circulated after meeting two.

While the content of this report is likely to vary between practices, pilot work indicated that the core practical recommendations were likely to include the practice (with support from the pharmacist) categorising eligible patients into one of the following groups:

1. Not prescribed a statin

2. Receiving simvastatin but dose suboptimal;

3. Receiving simvastatin 40mg;

4. Prescribed a statin other than simvastatin, optimal dose;

5. Prescribed a statin other than simvastatin, suboptimal dose.

In each case, cholesterol levels were controlled, uncontrolled or unchecked.

Appropriate actions will be mapped to each category of patient e.g. for those prescribed a suboptimal dose of simvastatin, the pharmacist will recommend each patient should receive a letter with a new prescription for simvastatin 40mg, barring contraindications. Based on the pharmacist’s impression of the practice’s repeat prescribing organisation and the willingness of GPs and nurses interviewed, the pharmacist will suggest who should be responsible for each agreed action. The pharmacist’s role in this process is to provide a concise summary of the evidence base and consensus opinion where required. Together with practice staff, the pharmacist will screen case notes, noting and recording the category of each patient and updating the practice’s disease register. Practices will be asked to continue the process of patient identification after the intervention period. In this way, eligible patients will include existing and incident patients.

The pharmacist will therefore plan appropriate actions and responsibilities for practice staff and match these to each category of patient. Table 2 describes options from a template plan.

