**3.3 Endpoints**

The primary endpoint is the proportion of patients with cholesterol controlled, evaluated at the level of the individual patient, in the SOS intervention arm practices compared with Usual Care (UC). Secondary endpoints are:

- Prescribing of simvastatin;
- Prescribing of Simvastatin 40mg with cholesterol control;
- Prescribing of simvastatin 40mg;
- Cholesterol tested since randomisation for patients prescribed simvastatin 40mg;
- Cholesterol levels of patients prescribed simvastatin 40mg;
- Cholesterol levels tested since randomisation;
- Cholesterol levels;
- Prescribing of any statin.

Outcomes will be assessed between 1.4 and 2.2 years (mean 1.7 years) after randomisation.

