Subgroup analyses of differences in endpoints between SOS and usual care groups will be defined by the following baseline variables: age, gender, practice level socioeconomic deprivation (≤ median, > median), practice type (single handed or group), patient type (prevalent: known to the practice at baseline or incident: new diagnoses after baseline date), number of co-morbidities (one vs. two or more), presence or absence of IHD, prescribed or not prescribed a statin and cholesterol controlled or uncontrolled at baseline.

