**3.8 Participating practices and patients**

Practices will be asked to identify patients who had confirmed vascular disease. These patients are at ≥ 30% risk of suffering a cardiovascular, cerebrovascular or peripheral vascular event in the next 10 years. In accordance with GG&C Cholesterol Guidelines (Appendix III), this level of risk will be confirmed by the following confirmed diagnoses:

- Myocardial infarction;
- CABG / angioplasty;
- Angina/IHD;
- Angiographic coronary artery disease;
- Stroke/transient ischaemic attack;
- Peripheral ischaemic arterial disease/intermittent claudication;
- Diabetic patients aged over 45years.

A validated computer search of each general practice’s computerised patient record will generate a list of eligible patients. Each patient’s computerized and paper record will then be screened to collect relevant data.

Due to time and resource limitations, a systematic sample of every third eligible patient’s data will be collected in 5 practices with the largest list sizes (12330, 7354, 7215, 7099 and 5616 patients). Therefore, cross sections of data will be collected at baseline. In addition, in all practices, some demographic data (in particular, the “Patient identification number”) may not be available. Both factors preclude longitudinal follow up of all patients. In all practices, data will be collected from each eligible patient’s record, anonymised in the practice and entered onto an ACCESS database.

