**4.1.2 Before the first meeting**

Pharmacists will be asked to work in their allocated practice one day each week for approximately one year. They plan to access, collect and summarise patient level information to confirm that each patient who is eligible for a statin is offered one, or is currently prescribed a statin, and if not, reasons recorded. This involves confirmation of eligible diagnoses, statin prescribing (current and historical), prescription ordering, cholesterol tests and levels. Practice disease registers will be validated and updated or amended where necessary. Confirmation of diagnoses will be sought by looking through case notes, computer records or hospital (including Accident and Emergency) discharge letters.

Reasons for patients not receiving a statin will be collected. From pilot work, these are likely to be due to failure of the practice to offer the patient a statin; the patient defaulting routine appointments; dropout from prescription ordering; a history of statin intolerance or contraindication. Some eligible patients may be overlooked by their practice. In this case, the pharmacist will be asked to reinstate the patient onto the relevant disease register, in order that they would be subject to routine call and recall for review by the practice, or contacted with the offer of statin initiation. In pilot work, pharmacists noticed that patients had moved house but the new address had not been entered onto the practice computer system, meaning the patient would not have received notification of the need for an appointment at the practice if a letter had been sent.

Pharmacists will be asked to use the time in the practice to collect and summarise eligible patient level information on diagnoses, statin prescribing history and cholesterol levels. Baseline information (collected prior to randomization) will be used as a starting point for this process. Pharmacists will be asked to identify prescribing traits and gaps in care e.g. lack of cholesterol levels which limited the practices’ ability to better manage eligible patients. The prescribing traits of individual GPs will be recorded whenever possible, to provide a rich source of information to individualise attempts to improve prescribing.

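### Who is counted at follow-up can depend on allocation, because only SOS practices receive pharmacist-led case finding and register amendment

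*Protocol*

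**What the plan says.** Protocol section 3.3 defines the outcome: "The primary endpoint is the proportion of patients with cholesterol controlled, evaluated at the level of the individual patient". Section 3.8 says how patients are found: "A validated computer search of each general practice’s computerised patient record will generate a list of eligible patients". Each patient's computerised and paper record is then screened. Because of sampling in the five largest practices and possibly missing identifiers, the same section concludes: "Both factors preclude longitudinal follow up of all patients".

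Section 4.1.2 describes the pharmacist's work in SOS practices. Diagnoses are confirmed from notes, computer records and discharge letters. On the registers it says: "Practice disease registers will be validated and updated or amended where necessary". Where a practice has overlooked an eligible patient, "the pharmacist will be asked to reinstate the patient onto the relevant disease register". Section 4.1.4 continues this through case-note screening, "noting and recording the category of each patient and updating the practice’s disease register", and asks practices to keep identifying patients after the intervention period: "In this way, eligible patients will include existing and incident patients". Section 4.2 gives usual care practices no pharmacist-led prescribing support during intervention or follow-up.

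Section 1.8 asks for data on incident as well as prevalent cases at baseline and follow-up. Section 3.5 lists, among subgroups said to be defined by baseline variables, "patient type (prevalent: known to the practice at baseline or incident: new diagnoses after baseline date"). It also lists statin prescription and cholesterol control at baseline.

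**The concern.** The endpoint is a proportion, so it changes when the list of patients changes, even if nobody's cholesterol does. The follow-up list comes from practice records, and in one arm only a pharmacist spends about a year checking and amending diagnostic information and prompting further case finding. Patients found in this way may differ from those already on the list in testing, treatment and control. This is post-randomisation identification bias: randomising practices does not protect against it, and adjusting for age and sex does not address list membership. No section limits the primary comparison to patients identified before randomisation, or makes follow-up case finding independent of the amended records.

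A second problem needs no assumption. Incident status arises after randomisation and so is not a baseline variable. For incident patients, and for patients who cannot be linked to the baseline extract, the subgroups by baseline statin and baseline control cannot be formed from collected baseline data.

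**Working it through.** **The plan's own figure.** The protocol gives no figure for list changes. Its one related calculation, the sample size in section 3.5, reproduces and is not in dispute. With ICC 0.4 and 40 patients per practice, the design effect is 1 + 0.4 × 39 = 16.6. For 50% versus 90% at two-sided 5% (alpha and power are assumptions, since neither is stated), 20 patients per arm before clustering give 80% power, and 20 × 16.6 / 40 = 8.3, so 9 practices. For 90% power, 26 × 16.6 / 40 = 10.79, so 11 practices. The stated 10 per group lies between. From this calculation only the 50% pilot rate is carried forward.

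**Does the denominator depend on arm?**
1. Eligible patients are those the record search finds and screening confirms (section 3.8, both arms).
2. Diagnoses and registers are worked on by a pharmacist in SOS practices only (sections 4.1.2, 4.1.4 and 4.2).
3. Patients diagnosed after baseline are in the analysis (sections 1.8 and 3.5).
4. There is no complete fixed cohort to anchor the comparison (section 3.8).

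Step 2 can therefore affect what step 1 returns at follow-up. The protocol does not say how often it does.

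**Illustration.** Assume no true effect, 50% control in both arms, and list changes in SOS only. Let f be the fraction added, r the fraction removed, and q the proportion controlled among those patients.

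Additions: SOS proportion = (0.50 + f × q) / (1 + f). For example, f = 0.20 and q = 0.20 give (0.50 + 0.04) / 1.20 = 0.45.

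| Added | q = 20% | q = 50% | q = 80% |
|---|---|---|---|
| 5% | 48.6% (OR 0.94) | 50.0% | 51.4% (OR 1.06) |
| 10% | 47.3% (OR 0.90) | 50.0% | 52.7% (OR 1.12) |
| 20% | 45.0% (OR 0.82) | 50.0% | 55.0% (OR 1.22) |

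Removals: SOS proportion = (0.50 - r × q) / (1 - r). With q = 20%, r = 5% gives 0.49 / 0.95 = 51.6% (OR 1.07) and r = 10% gives 0.48 / 0.90 = 53.3% (OR 1.14). With q = 50% the shift is zero.

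The sign depends on who enters or leaves, and the protocol does not settle that.

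**The case against.** The strongest reply is that the trial list is not the disease register. It comes from a validated search of the patient record, followed by screening, and this is described for every practice without regard to arm. Reinstating a patient on a register serves call and recall, and the protocol does not say that it alters what the search returns. This stands in part: the route from register work to trial list is inferred. But confirming diagnoses and continued case finding act on the same practice records that the search reads, and screening can only reject or confirm patients whom the search has found.

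Baseline data are collected before allocation and follow-up collectors are blinded (section 3.9). These protect how data are read, not which patients are listed. The prevalent/incident subgroup comes closer, but it is not the primary analysis. An overlooked prevalent patient reinstated in an SOS practice also fits neither class clearly.

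The protocol also argues deliberately for measuring both incident and prevalent patients (sections 1.8 and 2.4). That is a legitimate aim and a real cost of the fix. The analysis set might be defined further in a statistical analysis plan that is not shown, but the identification route and the subgroup label are fixed here.

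A reader might infer that SOS pharmacists rewrite the registers and delete wrong entries while usual care registers stay untouched. The text supports amendment where needed. It does not mention deletion, and it withholds only pharmacist-led support from usual care. Section 1.4.4 says that registers have been improving more generally.

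**Conclusion.** The concern holds as a risk of bias that the protocol leaves open, not as a demonstrated bias. Membership of the follow-up denominator can depend on allocation, and nothing in the protocol closes that route for the primary comparison. Under the stated assumptions (50% control, no true effect, an SOS list enlarged by 5% to 20%, and 20% to 80% control among added patients), the shift runs from about -5 to +5 points, with odds ratios from 0.82 to 1.22. It is zero if those patients match the list. The amount of change and the control rates are assumptions.

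A reader might infer that the bias favours SOS or could account for the expected effect. The documents support neither. Adding poorly controlled overlooked patients would work against SOS, and 5 points is one eighth of the 40-point difference used for sizing (50% to 90%). Nor is the median improvement of about 6% cited in section 1.3 a suitable yardstick, since it concerns prescribing and not cholesterol control.

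The labelling of incident status as a baseline variable is an error in the text whatever the size of the bias. The baseline-statin and baseline-control subgroups remain possible for patients with a baseline value.

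**What to change.** - Base the primary comparison on patients whose qualifying diagnosis was recorded in the practice record before the randomisation date, with the same date rule in both arms. At minimum, make this a named key sensitivity analysis of the primary endpoint. Use the date on which the diagnosis was entered, so that a diagnosis added later and back-dated does not qualify.
- Report incident and newly identified patients separately, as secondary.
- Report denominators, and numbers added or removed, by arm. The date rule deals with additions; it cannot restore a patient whose entry was later withdrawn, so removals need to be visible.
- Take patient type out of the list of baseline-variable subgroups, and limit the baseline-statin and baseline-control subgroups to patients with a collected baseline value.

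The cost is protocol wording and one extra date at extraction. The downside is that incident patients leave the main comparison, where the protocol wanted them, and the sample becomes slightly smaller. A key list held in each practice would allow the same patients to be re-extracted, but it is optional given the identifier and resource limits in section 3.8.

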**Table 2. Possible actions following a SOS intervention meeting**

| **Category of patient with vascular disease** | **Intervention by practice team (pharmacist, named nurse, named GP)** |
| --- | --- |
| Prescribed low potencystatin,§ cholesterol and LFTs known and at target | Switch to simvastatin 40mg by contacting on phone then confirming by letter |
| Prescribed low potency statin, cholesterol and LFTs not known/not at target | Letter for blood test then switch to simvastatin 40mg |
| Prescribed potent statin, cholesterol not at target | Phone call to discuss concordance |
| Prescribed potent statin, cholesterol and LFTs not known/not at target | Letter for blood test then increase dose if necessary |
| Prescribed potent statin, cholesterol at target | No action |
| Prescribed low potency statin, cholesterol at target | No action *  Check LFTs |
| No statin; LFTs and Cholesterol known | Letter for appointment for consideration of statin |
| No statin, LFTs and Cholesterol not known | Letter for appointment for bloods then discussion of need (GP/nurse), leading to Statin prescription |
| Started on simvastatin 40mg (or other sufficiently potent statin), cholesterol not known | Letter for appointment for bloods |

§ Potency relates to the cholesterol lowering ability of the statin. Low potency statins include Fluvastatin and Pravastatin. Potent statins are all others e.g. simvastatin, Atorvastatin, Rosuvastatin. * Some practices decided, on the weight of the HPS evidence base, to substitute low potency statins with simvastatin.

Pharmacists will quantify the number and confirmed the names and contact details (address, phone number) of patients fitting each category, then ask the practice to agree a follow up date and to name the person responsible for ensuring action.

Workload implications for the practice will be carefully considered by the pharmacist in advance of meeting two. Key anticipated actions include time to generate letters to eligible patients, setup a call/recall system, consultation time and time to enter new information onto the practice computer system to ensure long term follow up and sustainability of the changes. The pharmacist will anticipate these additional tasks and suggest ways to overcome them. Possible approaches include the practice dividing the list and allocating part of it to each GP to action, or reception staff agreeing to call patients for an appointment, booked for the GP during any quieter slots. The pharmacist will prepare an interactive plan on power point, with concise graphic material.

**4.1.5 Meeting 2**

Pharmacists will ask practices to protect approximately one hour for this meeting, to involve the whole practice because consensus building and agreement on next steps will require input from all practice staff. If one GP or nurse cannot make the meeting, the pharmacist will meet with each separately to cover the main educational points and practical decisions.

The objective is to gain firm commitment (from all individuals and the entire practice as a unit) on whether, when and how to phase a plan for systematic implementation of the guideline. Having thoroughly considered each part of the implementation plan in terms of workload implications, the pharmacist will deliver an interactive presentation including:

- The evidence base;
- A guideline summary;
- Anonymised patient specific prescribing and clinical data;
- Simulation of therapeutic challenges;
- A comparison of the practice’s prescribing trends with neighbouring practices;
- Opinion leaders’ answers to questions;
- Possible targets.

In the plan for change, the pharmacist will describe timelines; targets (anticipated improvements in prescribing, including tentative quantification of improved clinical outcomes for patients) and the benefits. Lower prescribing costs resulting from the changes will be anticipated and quantified. The pharmacist will offer help in steering, monitoring and feeding back progress on behalf of the practice.

All pharmacists will ensure their presentation adheres to the following points:

1. Agree clear educational objectives;

2. Agree clear behavioural objectives;

3. Present both sides of controversial issues;

4. Stimulate active participation;

5. Use concise graphics;

6. Highlight and repeat essential messages;

7. Obtain agreement and build on it;

8. Be enthusiastic;

9. Keep to allotted time.

**4.1.6 Between the second and third meetings**

Following the second meeting, pharmacists will use their time (one day per week), to implement change, reinforce and feedback through progress reports, until the agreed actions are carried out.

The pharmacists will record changes in prescribing at patient level. These data will be summarised and used in the presentation for the third meeting.

**4.1.7 Meeting 3**

The objectives of meeting three are to:

- Re-iterate key points agreed during meeting two;
- Enable two way feedback, consolidate and reinforce changes to prescribing;
- Address any ongoing implementation difficulties.

Pharmacists will try to meet one to one (face to face) with practice staff, at a time convenient to the GP or nurse. Pharmacists will be encouraged to provide feedback on any prescribing changes made in line with the agreement reached during meeting two. They will be asked to present statin prescribing of other (anonymised) practices over the same time period for comparison purposes. Reinforcement and repetition of key educational messages, reminders of agreed actions and open discussion of progress in relation to timescales will form key components of meeting three.

All pharmacists will leave meeting three with a firm commitment from the GPs and nurses to continue prescribing simvastatin 40mg for eligible patients.

**4.2 Usual Care**

Practices randomised into UC will receive no pharmacist-led prescribing support throughout the study period (intervention and follow up).

**5. Appendices**

**Appendix I**

## Heart Protection Study – Subgroups for 1st vascular event (CHD / CVA / revascularisation)

## Category N Placebo Simvastatin ARR NNT

Coronary Heart Disease 13386 27.5% 21.8% 5.7% 18

Any PVD 6748 32.7% 26.4% 6.3% 16

PVD alone 2701 30.5% 24.7% 5.8% 17

CVA (any stroke) 3280 29.8% 24.7% 5.1% 20

CVA (stroke alone) 1820 23.6% 18.7% 4.9% 20

Diabetes Mellitus (any diabetes) 5963 25.1% 20.2% 4.9% 20

Diabetes Mellitus (diabetes alone) 3982 18.6% 13.8% 4.8% 21

Total Cholesterol <5 4072 23.1% 17.7% 5.4% 19

Total Cholesterol 5 but <6 7883 24.5% 18.9% 5.6% 18

Total Cholesterol 6 8581 26.8% 21.6% 5.2% 19

ARR=absolute risk reduction; NNT=number needed to treat for 5 years to prevent one event

**Appendix II**

**
[figure not shown]
**

## Appendix III

## Secondary prevention of coronary heart disease and stroke

**Cholesterol**

##### Patients with established vascular disease are at high risk and should be treated with a statin regardless of total blood cholesterol concentration

##### i.e. Previous MI / pre- or post-CABG / pre- or post-Angioplasty / Angina / Angiographic coronary artery disease / Ischaemic stroke or TIA / Peripheral Arterial Disease / Diabetic patients aged  40 years

† *Discuss with lipid clinic if in doubt*

**Do within 24 hours of onset of acute MI*

**Random non-fasting test for total cholesterol*** **and LFT’s**

Consider secondary causes & familial hyperlipidaemia if Cholesterol >8.0 mmol/L†

***See BNF for cautions, contra-indications and clinically important interactions.***

# Re-test at 1 month

Random non-fasting total cholesterol + triglycerides + LFT’s

# Goals of Treatment by Three Months

# Total cholesterol concentration <5.00 mmol/l

# (<4.00 mmol/L for post CABG patients)

# and

# Reduce cholesterol concentration by  25%

Cholesterol Goals Achieved

Annual review to ensure continued concordance.

